# The PROMOTE study (High-protein and resistance-training combination in overweight and obesity) for short-term weight loss and long-term weight maintenance for Chinese people: a protocol for a pilot randomized controlled trial

**DOI:** 10.1186/s13063-019-3954-7

**Published:** 2020-01-08

**Keywords:** Obesity, Weight loss, Weight maintenance, Chinese population, Randomized controlled trial

## Abstract

**Background:**

It is very important for clinicians and dieticians to explore reasonable weight management strategies for obese people that address both short-term weight loss and subsequent weight maintenance. We hypothesized that resistance training combined with a high-protein diet would result in similar short-term weight loss but better long-term weight maintenance than either a conventional low-fat diet control or a high-protein diet alone.

**Methods/design:**

This is an 8-week randomized parallel controlled trial followed by a 24-week observational follow-up study. A 48-week supplementary follow-up study will be carried out if necessary. The study will be conducted between June 2019 and October 2020. The 90 overweight or obese participants will be randomly assigned to the conventional low-fat diet group, the high-protein diet group and the high-protein diet and resistance training combination group. Primary outcomes are body weight change at week 8 and week 24 compared with the baseline level.

**Discussion:**

High-quality research on the effect of a high-protein diet combined resistance training on weight loss and weight maintenance is limited in the Chinese population. Our study will provide a basis for obesity management in China and will promote the development of exercise- and diet-related studies.

**Trial registration:**

Chinese Clinical Trial Registry, ChiCTR1900023841. Registered on 14 June 2019.

## Background

Obesity and overweight currently affect about a third of the world’s population [1]. In total, 38% of adults are expected to be overweight and 20% to be obese by 2030 [2]. Obesity is linked to all metabolic-related diseases and is also associated with more than 200 different complications. For example, more than 80% of cases of diabetes can be attributed to obesity, and obesity is also associated with diabetes-related deaths. Overweight and obesity also increase tumor risk, and 40% of tumors in the United States were estimated to be caused by overweight and obesity in 2014 [3]. Obesity significantly increases the risk of death. The relationship between obesity and mortality has been evaluated in several large-scale epidemiological studies. For example, a meta-analysis of more than 30 million people in 230 cohort studies showed a significant increase in all-cause mortality rate with overweight and obesity [4, 5]. The treatment of obesity and obesity-related diseases also carries a huge economic burden. In addition to direct economic expenses, there are other costs such as loss of labor and decline in household income. It is therefore important and urgent for overweight and obese people to lose weight [6]. Weight loss can significantly decrease the incidence of obesity- and overweight-related diseases and the associated mortality, reduce the incidence of cardiovascular diseases [7], significantly delay the progress of impaired glucose tolerance to diabetes mellitus [8], and improve urinary incontinence, sleep apnea, depression, quality of life and physical function.

Obesity is a complex polygenetic condition that is affected by genetic, behavioral, socioeconomic and environmental factors, but it is preventable and treatable [9]. Medication and surgery are only recommended for specific groups, and the first-line treatment for obesity is diet management combined with exercise [10]. Many studies have shown that the right diet and exercise guidance can help obese and overweight people to achieve short-term weight loss. However, the recommended dietary guidelines for weight loss vary significantly and have been revised several times in different social groups, reflecting uncertainties in the field of obesity nutrition management and the difficulty of establishing a uniform recommendation for all social groups. Unfortunately, most people who successfully achieve short-term weight loss (about 70%) tend to regain at least 50% of the weight over the next 2 years and return to their previous weight levels within 3 to 5 years [11]. It is therefore very important for clinicians and dieticians to explore reasonable weight management strategies for obese people that address both short-term weight loss and subsequent weight maintenance [12–15].

A high-protein diet can provide sufficient satiety and food taste to resist the hunger caused by calorie restriction and can therefore increase compliance. Compared with a high-carbohydrate diet, a high-protein diet has a more significant thermic effect, which increases energy consumption [16]. A high-protein diet combined with resistance training can reduce the loss of fat-free body mass during weight loss and maintain a relatively high basal metabolic rate. It can also develop good dietary management habits and improve self-efficacy in the initial weight loss stage. This improvement in self-efficacy comes from enthusiasm for diet intake management and exercise. People with low self-efficacy tend to be more likely to give up and regain weight [17]. There have been a few international studies on short-term weight loss and long-term weight maintenance linked to a high-protein diet [18], but high-quality research on the effect of a high-protein diet on weight loss in the Chinese population is very limited [19]. More importantly, there are only a few international and Chinese studies on the role of resistance training in medium- and long-term weight maintenance, and the results are inconsistent [20–23]. We hypothesized that resistance training combined with a high-protein diet would result in similar short-term weight loss but better long-term weight maintenance than either a conventional low-fat diet control or a high-protein diet alone.

The objectives of this study were therefore: 1) to verify that a high-protein diet has a similar short-term weight loss effect as a traditional low-fat diet; 2) to verify that a high-protein diet combined with resistance training can achieve better medium- and long-term weight maintenance; and 3) to explore whether the improvement in self-efficacy and the ability for diet management during weight loss is a predictive factor for medium- and long-term weight maintenance.

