#### Outcomes

The primary outcome is body weight change at week 8 and week 24 compared with the baseline level.

Secondary outcomes include:
Change in body fat percentage at weeks 8 and 24 compared with the baseline levelChange in waist circumference at weeks 8 and 24 compared with the baseline levelThe proportion of participants who have successfully lost weight and been nonobese (defined as BMI <24 kg/m^2^) at weeks 8 and 24Diet management ability and weight loss perseverance at weeks 8 and 24Change in self-efficacy at weeks 8 and 24 compared with the baseline levelCompliance with the original diet plan at weeks 8 and 24Change in fasting blood glucose at weeks 8 and 24 compared with the baseline levelChange in fasting insulin level at weeks 8 and 24 compared with the baseline levelChange in blood pressure at weeks 8 and 24 compared with the baseline levelsIncidence of adverse events

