#### Statistical analysis

Epidata 3.1 (The EpiData Association, Odense, Denmark) will be used to manage data, and double data entry will be used to promote data quality. The primary and secondary outcomes will be analyzed based on the full analysis set. All outcomes will also be analyzed based on the per-protocol set. The security end point will be analyzed based on the safety analysis set. Supportive sensitivity analysis will be carried out based on the per-protocol and full analysis set using the method of last observation carried forward. Descriptive analysis will be conducted for continuous variables such as body weight, body fat percentage, blood glucose, blood lipids and blood pressure. Indexes such as the percentage of participants achieving effective weight loss will be summarized using frequencies and percentages. The adverse events and their incidence will be summarized. The mid-term analysis will be carried out at the end of the intervention, before the follow-up study.

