#### Determination of sample size

This study is an exploratory pilot study. In line with previous studies [18, 23], 30 participants in each group were initially scheduled to evaluate the efficacy of each group, whether more participants should be included, or whether the study should be stopped.

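### Objective 1 sets out to verify similar week-8 weight loss on a primary outcome, but no margin defines similar and the 30-per-arm exploratory pilot was not sized for equivalence

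*Protocol article*

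**What the plan says.** The Background lists as the first objective "to verify that a high-protein diet has a similar short-term weight loss effect as a traditional low-fat diet". The hypothesis in the same section extends the idea to the combination arm, which "would result in similar short-term weight loss but better long-term weight maintenance than either a conventional low-fat diet control or a high-protein diet alone". The Abstract repeats it. Study design defines the short term as 8 weeks.

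Under Outcomes: "The primary outcome is body weight change at week 8 and week 24 compared with the baseline level". Similarity at week 8 is therefore claimed on a primary endpoint.

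Three other sections bear on how the claim could be judged:

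- Study design says that body weight changes will be compared across the three groups at 8 weeks. It gives no criterion.
- Statistical analysis names the analysis sets and a last-observation-carried-forward sensitivity analysis, and says "Descriptive analysis will be conducted for continuous variables such as body weight". It also places a mid-term analysis at the end of the intervention.
- Determination of sample size says "This study is an exploratory pilot study" and gives the basis for the number: "In line with previous studies [18, 23], 30 participants in each group were initially scheduled".

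No section states a margin in kg or any other definition of similar.

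**The concern.** To verify that two diets have a similar effect is to claim equivalence. Such a claim has content only once the largest tolerable difference is named, because any finite sample leaves some range of differences open. Here that difference is not named in the objectives, where it would define the claim, or in the sample-size section, where it would drive the number.

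The wording also conflicts with the trial's own description. *Verify* is confirmatory language, while the sample-size section describes an exploratory pilot.

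At stake is the first half of the main hypothesis. If the week-8 interval is wide and includes zero, the protocol gives no rule for telling *the diets are alike* from *the trial could not tell*. A reader of the results could not tell either.

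**Working it through.** **What can be reproduced.** Three arms of 30 give 3 × 30 = 90, which agrees with the protocol. The 30 per arm cannot be derived, because no alpha, power, SD, expected difference, margin or dropout is stated.

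**Inputs.** n = 30 per arm (protocol). SD of week-8 weight change: 2, 2.5, 3 or 4 kg (assumed; the protocol gives none). Equivalence margins: 1, 1.5 or 2 kg (assumed, for illustration). The comparison is high-protein against low-fat.

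**Precision.** Standard error of the difference = SD × √(2/30) = 0.258 × SD. The 95% half-width is t(0.975; 58 df) × SE = 2.00 × SE. For SD 3: SE = 0.775 kg and half-width = 1.55 kg.

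**Chance that a real difference is non-significant.** This uses a noncentral t with 58 df and noncentrality (true difference)/SE, two-sided 5%. The protocol does not state this test. It serves only to show how uninformative a null result would be.

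| Assumed SD (kg) | 2 | 2.5 | 3 | 4 |
|---|---|---|---|---|
| 95% half-width (kg) | 1.03 | 1.29 | 1.55 | 2.07 |
| 90% half-width (kg) | 0.86 | 1.08 | 1.29 | 1.73 |
| Non-significant, true difference 1 kg | 52% | 67% | 75% | 84% |
| Non-significant, true difference 2 kg | 3% | 14% | 28% | 52% |

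**Chance of showing equivalence when the arms are truly equal.** Two one-sided 5% tests, that is, the 90% interval inside ± margin, by simulation:

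| Assumed margin | SD 2 | SD 2.5 | SD 3 | SD 4 |
|---|---|---|---|---|
| 1 kg | 21% | 2% | about 0% | about 0% |
| 1.5 kg | 78% | 49% | 21% | 0.4% |
| 2 kg | 97% | 84% | 64% | 21% |

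**Margin that 30 per arm supports.** For 80% power with truly equal arms, the smallest margin is about SE × (1.645 + 1.282). That is 1.5, 1.9, 2.3 and 3.0 kg at SD 2, 2.5, 3 and 4.

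**Reading.** Whether 30 per arm can support a similarity claim depends on the margin and the SD. The answer runs from almost never to almost always, and the protocol fixes neither quantity.

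**The case against.** The strongest reply is that this is a pilot, reported in a condensed article, with a statistical analysis plan that is not shown. The test, the model and the covariates may properly sit there, and their absence is no fault. The protocol does not declare an equivalence design. Its sample-size section says the data will inform whether to enrol more participants or stop, which is a legitimate pilot purpose. All of this stands. It excuses the lack of a power calculation. It does not excuse an objective worded as verification of similarity with the meaning of similar left open, and that mismatch is visible without the analysis plan.

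Four stronger readings are tempting, and the documents do not support them:

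- A reader might infer that body weight will only be described. Study design promises a between-group comparison at 8 weeks, and Statistical analysis says the primary outcome will be analysed on the full analysis and per-protocol sets. The accurate statement is that description is the only analysis named for body weight.
- A reader might infer that a non-significant result would automatically be reported as similarity. The protocol states no success rule, so this is a risk and not a stated plan.
- A reader might infer that 30 per arm is too few. With an SD of 2 to 2.5 kg and a 2 kg margin it would be enough (97% and 84%).
- A reader might take the 0.9 versus 0.3 kg in the Discussion as a benchmark of 0.6 kg. Those are 12-month meta-analysis figures, the 0.6 is a subtraction, and the protocol does not offer it as a week-8 effect.

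**Conclusion.** The point holds as a defect in how the objective is defined. A similarity claim on a primary outcome has no margin, and it sits in a self-declared exploratory pilot whose size was not derived for it. As written, objective 1 cannot be verified, because nothing separates evidence of similarity from an imprecise null result. The same applies to the combination arm's predicted short-term similarity to each of the other two arms.

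Under assumed SDs of 2 to 4 kg with all 30 per arm analysed, the week-8 difference would be known to within about ±1.0 to ±2.1 kg, and a true 1 kg difference would be non-significant in about 52% to 84% of trials. Dropout would widen the interval. These figures show scale only, since neither SD nor margin comes from the protocol, and they do not prove a shortfall in sample size.

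**What to change.** Choose one of two routes before the week-8 mid-term analysis.

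1. **Estimate.** Reword objective 1, and the short-term half of the hypothesis in the Abstract and Background, as estimating the between-group difference in week-8 weight change with its 95% confidence interval. Draw no similarity conclusion. This suits the pilot label and the stated use of the data for deciding on further enrolment.
2. **Test equivalence.** Fix and justify an equivalence margin in kg, apply it to each comparison for which similarity is claimed, and allow the word *similar* only if the 90% confidence interval of the difference lies inside the margin. Otherwise report the estimate and its interval without a similarity claim.

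The timing matters for the second route, because the trial is open-label and a margin set after week-8 results are seen would carry little weight.

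The cost is wording in the protocol and analysis plan, with no new data collection. The downside is that *similar* may not be claimable with 30 per arm, unless the SD is small or a wide margin can be justified.

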## Methods/design

### Study design

The PROMOTE study (High-protein and resistance-training combination in overweight and obesity) is an 8-week randomized parallel controlled trial followed by a 24-week observational follow-up study. A 48-week supplementary follow-up study will be carried out if necessary. The enrolled participants will be randomly assigned to the conventional low-fat diet group, the high-protein diet group, or the high-protein and resistance-training combination group, and changes in body weight, body fat and metabolic indexes will be compared between the three groups in the short term (8 weeks), the medium term (24 weeks) and the long term (48 weeks). The efficacy of the high-protein and conventional low-fat diets on weight loss, fat loss and improvement of various metabolic indexes will be evaluated and compared with the efficacy of the resistance training and high-protein diet combination. After 8 weeks of intervention, the participants will be strongly recommended to continue their diet and exercise plans until the achievement of individualized weight loss goals. During the following 24 or 48 weeks of observation, the participants’ diet management knowledge will be tested, their self-efficacy evaluated, and the proportion who continued to adhere to the plans will be observed. Finally, the relationship between diet management knowledge, self-efficacy and weight loss will be explored (Fig. 1).

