#### Intervention period

The participants’ baseline data will be collected, including body weight, body fat percentage and fat-free mass (using the Tanita TBF-300A Body Composition Analyzer, Tanita Europe, UK), waist circumference, hip circumference, systolic and diastolic blood pressure (Omron sphygmomanometer, Omron Healthcare Limited, Milton Keynes, UK), and a blood sample for the determination of blood glucose, blood lipids, renal function and insulin level. These will be collected in the morning after an 8-h fast.

During the 8-week intervention, the participants will receive dietary guidance, which varies by group, and prepare their own food following advice from the dietician. Participants in the resistance training group have to take part in resistance training at least three times a week. During the 8 weeks, the participants will receive face-to-face visits in weeks 2, 4 and 6, and their body weight, waist circumference, hip circumference, and systolic and diastolic blood pressure will be measured during each visit. The participant will receive telephone calls during weeks 1, 3, 5 and 7. During both visits and telephone calls, dietary and exercise guidance will be provided and recorded, and the MyFitnessPal diet inputs will be checked and recorded in written case report forms. The participants will also receive a face-to-face visit at the end of the 8-week intervention, and their body weight, body fat percentage and fat-free weight, waist circumference, hip circumference, and systolic and diastolic blood pressure will be measured, and blood samples taken for the determination of blood glucose, blood lipids, renal function and insulin levels. The participants’ self-efficacy will be investigated using the General Self-Efficacy Scale [24], and the diet management knowledge will be evaluated using a self-designed questionnaire.

During the intervention period the participants will not be allowed to add anything to their agreed intake (such as snacks and drinks) or to change their diet. If the participants wish to change their main meal for a particular reason (such as a social event), the investigator will be consulted by telephone to decide on the remedial measures required (such as reduction of calorie intake the next day). Any changes will be recorded using the MyFitnessPal record.

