### Efficacy assessments

Body weight is the primary outcome of this study and is selected as the main variable. Some important secondary variables with clinical significance are also selected for evaluation. Examinations conducted at each visit are shown in Table 1.

**Table 1 Tab1:** Study plan detailing the procedures

Study period	Screening	Intervention period								
Visit (V)	V1	V2	V3	V4	V5	V6	V7	V8	V9	V10
Study week	−1 (±2 days)	Randomization	1 (±2 days)	2 (±2 days)	3 (±2 days)	4 (±2 days)	5 (±2 days)	6 (±2 days)	7 (±2 days)	8 (±2 days)
Telephone visit			√		√		√		√	
Screening/demography/baseline										
Written informed consent	√									
Inclusion/exclusion criteria	√	√								
Demographics	√									
Physical examination, height, and weight	√									
Medical/ current conditions	√									
History of diabetes and complications	√									
Intervention										
Instruction of diet and exercises		√	√	√	√	√	√	√	√	
Vital signs (blood pressure, heart rate)	√	√								√
Body weight	√	√	√	√	√	√	√	√	√	√
Waist circumference, hip circumference	√	√	√	√	√	√	√	√	√	√
Body fat percentage, lean body mass		√								√
Hematology panel		√								√
Urinalysis		√								√
Liver function		√								√
Creatinine, uric acid		√								√
Lipids		√								√
Glucose, insulin		√								√
Adverse events		√	√	√	√	√	√	√	√	√
Diet management knowledge										√
Self-efficacy scale		√								√

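### Objective 3 needs the improvement in diet-management ability during weight loss, but the only questionnaire named for it has no baseline administration

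*Protocol article*

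**What the plan says.** Objective 3 (Background) looks ahead to weight maintenance in the medium and long term and asks "whether the improvement in self-efficacy and the ability for diet management during weight loss is a predictive factor".

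Two instruments are named. Self-efficacy is measured with the General Self-Efficacy Scale. For diet management, the Intervention period section says, in describing the visit at the end of the 8 weeks, that "the diet management knowledge will be evaluated using a self-designed questionnaire".

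Table 1 (Efficacy assessments) gives the timing within the intervention. The row "Self-efficacy scale" is ticked at V2 (randomization) and V10 (week 8). The row directly above it, "Diet management knowledge", is ticked at V10 only.

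For the observation period, Study design says that participants' "diet management knowledge will be tested, their self-efficacy evaluated". The Outcomes section lists self-efficacy as a change from baseline at weeks 8 and 24. It lists diet-management ability at the same two times, without reference to a baseline.

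**The concern.** The objective names improvement as the predictor, and the schedule gives one of its two components a starting value and the other none. Without a starting value, a participant who knew a great deal about diet on entry and learned nothing cannot be told apart from one who knew little and learned a great deal.

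At stake is what an association between the week-8 score and later weight would mean. It could reflect what participants brought with them rather than what they acquired during the intervention. The objective is about acquisition. The Background and Discussion also argue that habits formed in the early weight-loss stage protect against regain.

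The gap cannot be closed afterwards for a given participant. Table 1 starts diet and exercise instruction at V2, and once that has begun the pre-intervention level can no longer be measured.

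**Working it through.** The plan gives no figure to reproduce. The check compares the measurement times with what the objective requires.

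**Measurement times**

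| Time | Self-efficacy scale | Diet-management questionnaire |
|---|---|---|
| V1 (screening) | none | none |
| V2 (randomization) | yes (Table 1) | none |
| V3 to V9 (weeks 1 to 7) | none | none |
| V10 (week 8) | yes (Table 1) | yes (Table 1; Intervention period) |
| Observation period, including week 24 | planned (Study design; Outcomes) | planned (Study design, as knowledge; Outcomes, as ability) |

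**What the objective needs**

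For each participant, improvement during weight loss = score at V10 − score at V2.

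- Self-efficacy: both terms are scheduled, so the change can be computed.
- Diet management: the V2 term is not scheduled, so the change cannot be computed.

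**Count**

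The sample-size section states that "30 participants in each group were initially scheduled to evaluate the efficacy of each group". With three groups, 3 × 30 = 90 participants.

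- As scheduled, 0 of 90 have a V2 questionnaire score, so 0 of 90 have a change score.
- With the questionnaire also given at V2, up to 90 of 90 would have one before missing data. If m participants were randomized before the change, the maximum is 90 − m. The article does not state m.

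**Why the week-8 score does not stand in for the change**

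Write S2 and S10 for the scores at V2 and V10, D = S10 − S2 for the improvement, and Y for later weight maintenance. Since S10 = S2 + D,

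Cov(S10, Y) = Cov(S2, Y) + Cov(D, Y).

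The schedule yields only the left-hand side. Objective 3 asks about the second term on the right, and without S2 the two terms cannot be separated.

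**Whether another interval could serve**

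A change from week 8 to week 24 could be computed from the planned follow-up testing. It begins after the intervention has ended and overlaps the maintenance period it is meant to predict, so it is not improvement during weight loss.

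**The case against.** The best defence is that objective 3 can be parsed differently: improvement in self-efficacy on one side, and the ability for diet management, as a level, on the other. The Outcomes section and Table 1 fit this, because both treat self-efficacy as a change and diet management as a level. The exploratory analysis in Study design, relating knowledge, self-efficacy and weight loss, needs no change score either. On that parsing the schedule is consistent. It is a possible reading but the less natural one, given a rationale built on habits formed during the initial stage. If it is what was meant, the objective should say so, so the text needs attention in either case.

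A second objection is that ability and knowledge are different words, used in different sections and never linked. Daily diet records in the smartphone application start in the run-in period, so some pre-intervention diet data will exist. This stands to the extent that the count of 0 of 90 applies to the questionnaire score. The article does not designate the diet records as the measure of ability, and the questionnaire is the only instrument it names.

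A third is that the objective is exploratory and the trial a pilot, and that a week-8 level may predict maintenance whatever its origin. That is fair, and it limits the weight of the point. It does not make a level into an improvement.

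Three stronger inferences are tempting, and the document does not support them:

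- **The questionnaire is used at week 8 and never again.** This is true only within the intervention schedule of Table 1. Study design and Outcomes both plan later assessment.
- **The baseline list in the Intervention period section proves the omission.** That list ("baseline data will be collected, including body weight, body fat percentage and fat-free mass") is introduced as non-exhaustive and also leaves out self-efficacy, which Table 1 does schedule at V2. Table 1 carries the point.
- **Both instruments are missing at the end of follow-up because the visit description there names neither.** Table 1 as shown ends at V10, the article is a condensed account, and other sections state that both will be assessed. That silence is not evidence of a gap.

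**Conclusion.** The point holds in a limited form. The diet-management questionnaire has no baseline administration, so improvement over the 8-week weight-loss phase cannot be computed from it for any of the 90 planned participants, and the diet-management half of objective 3 cannot be answered as written.

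This rests on two readings: that improvement in the objective governs both constructs, and that the knowledge questionnaire is the measure of diet-management ability. Both are the natural readings, but neither is stated outright.

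A reader might infer that objective 3 as a whole fails. It does not: the self-efficacy half has its baseline. The primary outcome and objectives 1 and 2 do not depend on the questionnaire. This is an inexpensive improvement to an exploratory objective and not a threat to the trial's main comparisons.

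**What to change.** Add a tick at V2 in the Table 1 row for diet management knowledge and give the same questionnaire there, before the assignment is disclosed and before diet instruction begins. Use the V2-to-V10 change in score as the diet-management predictor in objective 3, and state that the knowledge questionnaire is the measure of ability.

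For participants already randomized without a baseline score, report the week-8 level only, and state how many participants contribute a change score.

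If testing at V2 is not feasible, restate objective 3 to use the week-8 level of diet-management knowledge, and do not interpret that level as improvement.

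The cost is a few minutes per participant at a visit where the self-efficacy scale is already given. The remaining downside is missing baseline scores for those already enrolled. The Trial status section describes recruitment as under way since June 2019 and expected to run to October 2020, so the number lost depends on how soon the change is made.
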